## Methods/design

### Study design

The PREPARED Trial is a 4-year cluster randomized trial. The PREPARED Trial intervention will be implemented at the LTCF level. To reduce potential contamination between intervention and control study arms by nursing staff members who may provide replacement hours of employment at different units/floors within their LTCF, a cluster design was adopted such that participating LTCFs (clusters) will be assigned to either the PREPARED Trial intervention or the control (usual care) arm of the study. Nursing staff and LTC residents meeting trial inclusion criteria from all arms will be enrolled in the study. Residents will be followed for an 18-week period or until death or transfer to another facility.

A cluster randomized trial parallel design, employing a covariate constrained randomization (CCR) procedure [30, 31], will be used to allocate LTCFs, rather than individual residents, to either the intervention or control study arm. Cluster randomized trials typically use clusters as the main unit of analysis, given that the intervention is conducted at the cluster level (in the current study, the LTCFs are the clusters). However, given that the number of clusters is usually much smaller than the total number of participants, a simple cluster randomization or a procedure based on stratification may yield study arms that are imbalanced and differ on key baseline cluster characteristics. A CCR approach will be used to address this issue, as it specifically aims to balance the distribution of important cluster characteristics or covariates across study arms [30–32]. In addition, given the need to assess each resident weekly for a follow-up period of 18 weeks and the logistical limitations (large geographical coverage, 45–50 LTCFs included, and limited work force) involved in such a trial, we will employ a sequential approach whereby sets of clusters (LTCFs) will be randomized into the two study arms in consecutive trial ‘cycles’ lasting 20 weeks each, including the two-week screening period before enrolment (see Fig. 1 for a breakdown of research activities within a study cycle).

**Fig. 1 Fig1:**
[figure not shown]
Timeline of Research Activities per Trial LTC Facility

This 18-week period was selected using data from one of the precursor delirium studies conducted in this population, which found that 97% of all incident episodes of delirium among cognitively impaired residents occurred within the first 18-weeks of follow-up [33]. Research staff will visit each facility to enroll eligible residents and to conduct follow-up assessments. Data will also be abstracted from resident charts and existing LTCF databases.

### Participants

Participants for this study will include LTC residents (who will be assessed for delirium, cognition, functional autonomy, and other clinical/demographic variables) and nursing staff members (who will provide data pertaining to the resident population and/or implement the intervention). No monetary incentives will be provided to remunerate participation. Participating LTCFs will include public and semi-private residential LTCFs in and around Montreal, Quebec that provide residence to elderly individuals requiring specialized care per day, including assistance with one or more basic activities of daily living beyond that which can be provided in a community setting [34, 35]. Institutions will only be eligible if they provide 24-h of supervised nursing care (i.e. an RN is on site 24 h per day), including professional health services and personal care.

All Registered Nurses (RNs), Licensed Practical Nurses (LPNs) and personal support workers (PSWs) working during the day shift will be eligible to participate if they: 1) are working at least 3 days/week on the same nursing unit (i.e. are not ‘floating’ between units); and 2) have worked at the LTCF for at least 1 month prior to the follow-up start date at their site.

Residents will be enrolled based on a series of inclusion/exclusion eligibility criteria. In order to be included, residents must: be 65 years or older; have dementia and/or cognitive impairment, as determined by discussions with the nursing staff and chart abstraction; have a minimum length of stay in the LTC facility of at least 2 weeks prior to the start of the baseline assessments; be at risk of delirium, as indicated by a score of 1 or higher on a validated 5-item delirium risk screening tool [36] (Fig. 2); and be delirium-free at baseline, as assessed by the Confusion Assessment Method (CAM) [37, 38], the Delirium Index (DI) [39], and a brief chart review over a period of two consecutive weeks immediately preceding the start of the follow-up period. Residents will be excluded if they are: unable to communicate verbally (as determined by either the nursing staff or two consecutive 0-score administrations of the composite cognitive interview, which is part of the CAM procedure); unable to communicate verbally in English or French; have a history of specific psychiatric conditions (bipolar disorder, depression with signs of psychosis, and psychotic disorders) or intellectual disability [40, 41]; or are being provided with end-of-life or palliative care.

**Fig. 2 Fig2:**
[figure not shown]
Delirium Risk Screening Tool and Decision Tree

### Sample size calculation

Based on sample size calculations, we plan to recruit between 400 and 600 LTC residents in the current study. Sample size was computed for our primary objective, to detect any differences between our intervention and control trial arms in the incidence of a first delirium episode after 18 weeks of follow-up. We used the Freedman log-rank test method to compare two survivor functions at the end of study follow-up. In a post-hoc secondary analysis of the precursor LTC delirium study, for which we applied the PREPARED Trial inclusion and exclusion criteria [33], we obtained incidence rates that we assume will be experienced by our control group, namely 3.75 cases per 100 person-weeks. We tested different scenarios concerning the size of our sample after 18 weeks of follow-up from baseline. We also tested our assumptions regarding the magnitude of our intervention effect by allowing the reduction in incidence rates to vary between 30 and 73%, as previous studies (in non-LTC settings) have reported this range in variation [1, 18–22]. Using methods of estimation ‘uncorrected’ for cluster randomization, we found that including 180 residents per trial arm (after assuming a 15% rate of attrition over our 18 week follow-up period to account for deaths, transfers and drop-outs) will enable us to detect a 40% reduction in the incidence of delirium (HR = 0.6) with a power of 80% at the 5% level (assuming 2-tailed test and equal group size).

The ‘corrected’ sample size for cluster randomization was then computed according to Rutterford et al. (2015) [42], where a design effect was incorporated that inflated the preliminary uncorrected calculation [43]. This design effect depends on two variables: 1) the Intra-cluster Correlation Coefficient (ICC) and 2) the number of clusters, where the total estimated required sample size is directly proportional to the magnitude of ICC and inversely proportional to the total number of clusters participating in the trial. Our sample size analysis, therefore, provides estimates using two conservative values for our expected outcome, and incorporates scenarios for both ICC and the number of clusters (or LTC facilities) that will be included in the study (Fig. 3).

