**Fig. 3 Fig3:**
[figure not shown]
PREPARED Cluster Randomized Trial Sample Size Estimation

For the purpose of this protocol, we began with an estimated ICC derived from the 2011 Quebec delirium study post-hoc analysis described above. In this dataset, when considering the three facilities that would be representative of the clusters or LTCFs participating in the PREPARED Trial, we found an ICC of 0.06. This estimate should be regarded as quite conservative, given that this ICC was computed using a total of only 3 clusters, whereas our study will be approximately 15 times larger in terms of total cluster size. The number of clusters per arm in our study will vary between 20 (worst case scenario) and 25 (best case scenario). Before performing our CCR procedure, recruited RNs will each be asked to provide the study team with the maximum number of participants that they would be willing to manage as trial participants under the assumption that theirs could be an intervention site. Given that we know a priori that our clusters are likely to be unequal in size, our randomization procedure will use this nurse-to-resident participant ratio as a CCR variable to balance the ratio of intervention-to-control participants in our trial. It should be noted that the range of sample size required varies greatly by ICC: from 864 study subjects within 50 clusters in order to detect a minimum HR of 0.6 in our worst case scenario of an ICC of 0.1, to approximately 300 subjects for HR of − 0.55 and an ICC of 0.02. As such, we plan to enroll about 200–300 residents per intervention arm, for a total enrollment of 400–600 residents, which will account for a liberal 15% estimate for participant attrition. Computations for the above sample size calculations were performed using STATA version 13.0.

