### Enrollment and randomization procedure

To ensure a manageable workload for the LTCF nursing staff, the study will enroll only as many residents per team as the participating day shift RN deems to be reasonable. This number will be determined on an individual basis, and will constitute a contract between the research team and the LTCF RN.

Residents who have consented to participate will undergo a two-week delirium prevalence screening using the CAM and the DI (see assessments below) [37–39]. Residents who are delirium-free throughout this two-week period will be randomized for inclusion in the study. The number randomized per unit will be consistent with the number agreed upon by that specific unit nurse.

Residents will be randomized using an electronic data management (EDM) platform provided by the Information Management Services Unit (IMS) at McGill University/Lady Davis Institute of the Jewish General Hospital. IMS will employ simple random sampling, a basic sampling technique where a subset of individuals (a sample) is selected from within a larger set of individuals (a population). In such a method, each individual is chosen entirely by chance, and each member of the population has an equal chance of being included in the sample.

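### The cluster-corrected sample sizes assume equal LTCFs although the article expects unequal ones, so they give somewhat less than the implied 80% power

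*Protocol article*

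**What the plan says.** All of this is in the Protocol article.

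- **Sample size calculation, before clustering.** The target is the "incidence of a first delirium episode after 18 weeks of follow-up". The control rate is taken from a precursor study, "namely 3.75 cases per 100 person-weeks". With 180 residents per arm, after 15% attrition, the trial can "detect a 40% reduction in the incidence of delirium (HR = 0.6"). The test is two-sided at 5%, with 80% power and arms of the same size.
- **Sample size calculation, correction for clustering.** A design effect is applied. It is said to rest on two quantities, the ICC and the number of clusters, with the required total "directly proportional to the magnitude of ICC and inversely proportional to the total number of clusters".
- **Same section, text after Fig. 3.** The expected ICC is 0.06, with 20 to 25 clusters per arm. The required size runs "from 864 study subjects within 50 clusters in order to detect a minimum HR of 0.6" at ICC 0.1 down to about 300 at HR 0.55 and ICC 0.02. Planned enrolment is 400–600.
- **Same text, on cluster size.** "Given that we know a priori that our clusters are likely to be unequal in size", the nurse-to-resident ratio is used as a variable in the covariate constrained randomization (CCR), to balance participant numbers between arms.
- **Enrollment and randomization procedure.** This gives the reason for the inequality: "the study will enroll only as many residents per team as the participating day shift RN deems to be reasonable".

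**The concern.** A design effect built only from the ICC and the number of clusters treats every LTCF as contributing the same number of residents. The article says this will not happen. For a given total and a given number of clusters, unequal sizes reduce the effective sample size, and the reduction grows with the ICC. The stated remedy works between arms: balancing a ratio in CCR makes the arm totals similar. It leaves the spread of LTCF sizes within each arm as it was, and that spread causes the loss.

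If the printed sizes carry no allowance for this, they fall short of the 80% power they imply. The shortfall would be largest at the higher ICCs and with fewer LTCFs.

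**Working it through.** **Inputs from the article:** two-sided 5%, 80% power, 1:1 allocation, HR 0.6, control rate 0.0375 per person-week, 18 weeks, 15% attrition, Freedman log-rank, ICC 0.02 to 0.1, 40 or 50 LTCFs.

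**Input assumed:** CV of LTCF size 0.3 to 0.6. The article gives none.

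**1. Uncorrected size.**
- Events = (1.960 + 0.842)² × [(1 + 0.6)/(1 − 0.6)]² = 125.6.
- Control survival = exp(−0.0375 × 18) = 0.509; intervention survival = 0.509^0.6 = 0.667; mean event risk = 0.412.
- Residents = 125.6/0.412 = 304.9, or 153 per arm. 153/0.85 = 180 per arm, as printed.

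**2. Printed cluster-corrected sizes.**
- HR 0.6, ICC 0.1, 25 clusters per arm, equal sizes: residents per cluster = 153 × 0.9/(25 − 153 × 0.1) = 14.2. Rounded up to 15, the design effect is 1 + 14 × 0.1 = 2.4, and 2 × 180 × 2.4 = **864**, as printed. The rounding up is my inference; without it the formula gives 827 to 835.
- HR 0.55, ICC 0.02, 25 clusters per arm, equal sizes: 296 to 298, against the printed figure of about 300.
- A hidden allowance does not fit both figures. A CV near 0.34 could give 864 only if attrition were left out, and the second figure would then be about 255.

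**3. Adding size variation.** With mean analysed cluster size m:

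DE = 1 + [(1 + CV²)m − 1] × ICC

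For K clusters and n = 304.9, the required total is N = n(1 − ICC)/[1 − n × ICC × (1 + CV²)/K]/0.85.

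Required N, HR 0.6, ICC 0.06:

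| LTCFs | CV 0 | 0.3 | 0.4 | 0.5 | 0.6 |
|---|---|---|---|---|---|
| 50 | 532 | 561 | 586 | 621 | 671 |
| 40 | 621 | 672 | 718 | 787 | 892 |

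**4. Power.** Effective events d = 0.85N × 0.412/DE, and z = √d × (1 − 0.6)/(1 + 0.6) − 1.960. Example: N = 600, ICC 0.06, 50 LTCFs, so 510 residents analysed and m = 10.2.
- CV 0: DE = 1.552, d = 135.4, z = 0.949, power 82.9%.
- CV 0.6: DE = 1.772, d = 118.5, z = 0.762, power 77.7%.

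The formula in step 3 weights residents equally whatever the size of their cluster, so it is conservative. If the analysis weights clusters optimally, the effective sample is K × E[mᵢ/(1 + (mᵢ − 1) × ICC)], where mᵢ is the size of cluster i. I computed this with gamma-distributed sizes, which is also an assumption.

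| Scenario (HR 0.6) | Equal sizes | CV 0.3 to 0.6, conservative | CV 0.3 to 0.6, optimal weights |
|---|---|---|---|
| N = 600, ICC 0.06, 50 LTCFs | 82.9% | 81.6–77.7% | 82.1–79.8% |
| N = 600, ICC 0.06, 40 LTCFs | 79.2% | 77.7–73.1% | 78.4% to about 76% |
| N = 864, ICC 0.1, 50 LTCFs | 80.7% | 78.5–72.4% | 79.8–77.3% |
| N = 400, ICC 0.02, 50 LTCFs | 80.0% | 79.5–78.3% | smaller loss |

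**5. The proportionality wording.** With equal clusters, HR 0.6 and K = 50, a fivefold ICC (0.02 to 0.1) takes N from 400 to 827, which is 2.1-fold. At ICC 0.1, going from 40 to 50 LTCFs takes N from 1,357 to 827, a 39% cut; strict inverse proportionality would give 20%. The direction is right, but neither relation is proportional.

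**The case against.** - **The usual formula overstates the loss.** The Statistical data analysis section plans regression models and reports an ICC. This suggests clustering will be modelled, although no model is named. Such models down-weight large clusters. This stands, and it is why both columns are shown: with optimal weights, 600 residents in 50 LTCFs at ICC 0.06 still give about 80% over the whole assumed CV range.
- **The CV is assumed.** This stands. At CV 0.3 that same scenario loses only 0.8 to 1.3 points.
- **The ICC matters more.** This stands. With equal clusters, the ICC range alone moves the required total from 400 to 827. At ICC 0.06 with 50 LTCFs, 400 residents give 72.2% before any size variation.
- **Mean cluster size is also missing from the sentence.** That is no error: with the number of clusters fixed, it follows from the total.

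A reader might go further and infer that the article overstates a printed power for 400–600 residents. It does not. Its only stated power is 80% for the uncorrected 180 per arm; for the corrected sizes 80% is implied. A reader might also take the proportionality sentence for a calculation error. No printed figure is derived from it, so it is loose wording.

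None of this shows that size variation was allowed for.

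**Conclusion.** The point holds at moderate size. The text and both printed totals point to an equal-cluster design effect, while the article itself expects unequal clusters; balancing the arms does not repair that. The corrected sizes therefore give somewhat less than the 80% they imply.

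Over an assumed CV of 0.3 to 0.6 and HR 0.6, the loss at the article's own ICC of 0.06 with 600 residents is:
- 50 LTCFs: 1.3 to 5.2 points by the conservative formula, 0.8 to 3.1 with optimal weights.
- 40 LTCFs: 1.5 to 6.1 points by the conservative formula, and roughly half that with optimal weights.

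At the printed 864 (ICC 0.1) it is 2.2 to 8.3 points, or 0.9 to 3.4. At ICC 0.02 it is about 2 points or less.

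By the conservative formula with 50 LTCFs, the required total passes the 600 ceiling between CV 0.4 and 0.5. With optimal weights it does so only near CV 0.6 (605). With 40 LTCFs it is above 600 even for equal clusters (621), so that shortfall is not caused by size variation.

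Fig. 3 could not be seen. The conclusion rests on the section's text and the two printed totals.

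**What to change.** 1. Add a cluster-size term to the design effect, DE = 1 + [(1 + CV²)m − 1] × ICC, with a stated planning range for the CV **at LTCF level**. Label the formula conservative.
2. Restate the required total, and the power at 400, 500 and 600 residents, as ranges over ICC, number of LTCFs and CV.
3. Update the CV as cycles accrue, using LTCF-level totals of the nurse-declared numbers. Those declarations cannot supply the planning value: they are ceilings set by individual nurses, and LTCFs are randomized in successive cycles, so the full set is not known at the outset.
4. Replace the two proportionality phrases with wording that the required size increases with the ICC and decreases with the number of clusters.

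The cost is a short recalculation and slightly less favourable stated figures. No extra residents are proposed.

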**Fig. 3 Fig3:**
[figure not shown]
PREPARED Cluster Randomized Trial Sample Size Estimation

For the purpose of this protocol, we began with an estimated ICC derived from the 2011 Quebec delirium study post-hoc analysis described above. In this dataset, when considering the three facilities that would be representative of the clusters or LTCFs participating in the PREPARED Trial, we found an ICC of 0.06. This estimate should be regarded as quite conservative, given that this ICC was computed using a total of only 3 clusters, whereas our study will be approximately 15 times larger in terms of total cluster size. The number of clusters per arm in our study will vary between 20 (worst case scenario) and 25 (best case scenario). Before performing our CCR procedure, recruited RNs will each be asked to provide the study team with the maximum number of participants that they would be willing to manage as trial participants under the assumption that theirs could be an intervention site. Given that we know a priori that our clusters are likely to be unequal in size, our randomization procedure will use this nurse-to-resident participant ratio as a CCR variable to balance the ratio of intervention-to-control participants in our trial. It should be noted that the range of sample size required varies greatly by ICC: from 864 study subjects within 50 clusters in order to detect a minimum HR of 0.6 in our worst case scenario of an ICC of 0.1, to approximately 300 subjects for HR of − 0.55 and an ICC of 0.02. As such, we plan to enroll about 200–300 residents per intervention arm, for a total enrollment of 400–600 residents, which will account for a liberal 15% estimate for participant attrition. Computations for the above sample size calculations were performed using STATA version 13.0.

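### The text gives no cluster-corrected power for the planned 400–600 residents; at the protocol's own ICC of 0.06 most of that range falls short of 80% for HR 0.6, and the worst case of 864 assumes the best-case number of facilities

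*Protocol article*

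**What the plan says.** All of this is in the Protocol article, Sample size calculation, including the paragraph below Fig. 3.

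- The calculation is for the "incidence of a first delirium episode after 18 weeks of follow-up". The control rate is "namely 3.75 cases per 100 person-weeks", and the method is given as: "We used the Freedman log-rank test method to compare two survivor functions at the end of study follow-up".
- Without cluster correction and with 15% attrition included, 180 residents per arm are said to "detect a 40% reduction in the incidence of delirium (HR = 0.6) with a power of 80"%, two-sided at 5%.
- A design effect is then applied. It is described as depending on the ICC and the number of clusters. The ICC estimated from three facilities of the precursor study is 0.06, which the authors regard as conservative.
- On clusters: "The number of clusters per arm in our study will vary between 20 (worst case scenario) and 25 (best case scenario").
- On cluster sizes: "Given that we know a priori that our clusters are likely to be unequal in size".
- The text quotes two corrected totals. One runs "from 864 study subjects within 50 clusters in order to detect a minimum HR of 0.6 in our worst case scenario", with ICC 0.1. The other is about 300 for an HR of 0.55 with ICC 0.02.
- The conclusion follows directly: "As such, we plan to enroll about 200–300 residents per intervention arm, for a total enrollment of 400–600 residents", attrition included.

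**The concern.** The quoted totals, 864 and about 300, sit at ICC 0.1 and ICC 0.02. The section's own estimate, 0.06, lies between them, and the text gives no total for it. The move to 400–600 is therefore not tied to any stated combination of HR, ICC and number of facilities. The only power a reader can carry forward is the uncorrected 80% for HR 0.6.

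The largest total is also labelled the worst case, yet it uses 50 facilities, which is the number the same paragraph treats as most favourable.

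This is the sizing of the primary outcome. If enrolment ends near 400 and the result is null, readers need to know that the chance of missing HR 0.6 was about 30% at the protocol's own ICC, not 20%.

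**Working it through.** **Inputs (Sample size calculation).** Control rate 0.0375 per person-week; 18 weeks; Freedman log-rank; HR 0.6 or 0.55; 80% power; two-sided 5%; 1:1 allocation; 15% attrition; ICC 0.02, 0.06 or 0.1; 20 to 25 facilities per arm. A total of 45 is treated as 22.5 per arm on average. Cluster sizes are equal unless stated.

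**1. Reproduce the uncorrected size.**
- Event-free at 18 weeks: control exp(−0.0375 × 18) = 0.509; intervention exp(−0.6 × 0.675) = 0.667.
- Events = (1.960 + 0.842)² × ((1 + 0.6)/(1 − 0.6))² = 7.849 × 16 = 125.6.
- Completers = 2 × 125.6/(2 − 0.509 − 0.667) ≈ 305, or 152.4 per arm.
- Enrolled = 152.4/0.85 = 179.3 per arm, which matches 180.

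**2. Reproduce the corrected sizes.** With k clusters per arm and n uncorrected completers per arm, the corrected completers per arm are n·k·(1 − ICC)/(k − n·ICC).
- HR 0.6, ICC 0.1, k = 25: 152.43 × 25 × 0.9/(25 − 15.243) = 351.5 per arm, or 14.06 per cluster. Rounded up to 15, the design effect is 1 + 14 × 0.1 = 2.4, and 360 × 2.4 = 864, an exact match. Unrounded, 2 × 351.5/0.85 = 827.
- HR 0.55, ICC 0.02: 296 to 303 enrolled across 50 to 40 clusters, which matches about 300.

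**3. Size needed for HR 0.6 at ICC 0.06.**

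| Facilities | Completers per arm | Enrolled total | With whole cluster size m: 360 × (1 + (m − 1) × 0.06) |
|---|---|---|---|
| 50 | 152.43 × 25 × 0.94/(25 − 9.146) = 225.9 | 532 | m = 10: 554 |
| 45 | 152.43 × 22.5 × 0.94/(22.5 − 9.146) = 241.4 | 568 | m = 11: 576 |
| 40 | 152.43 × 20 × 0.94/(20 − 9.146) = 264.0 | 621 | m = 14: 641 |

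**4. Power of the planned enrolment.** Power = Φ(√E × (1 − HR)/(1 + HR) − 1.96), where E is completers divided by the design effect, times the mean event probability (0.412 for HR 0.6).

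Example, 400 enrolled in 40 facilities at ICC 0.06: 340 completers; 8.5 per cluster; design effect 1 + 7.5 × 0.06 = 1.45; E = 340/1.45 × 0.412 = 96.6; Φ(9.83 × 0.25 − 1.96) = 0.69.

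| HR, ICC | Enrolled | 40 facilities | 45 | 50 |
|---|---|---|---|---|
| 0.6, 0.06 | 400 | 69% | 71% | 72% |
| 0.6, 0.06 | 500 | 75% | 77% | 78% |
| 0.6, 0.06 | 600 | 79% | 81% | 83% |
| 0.6, 0.02 | 400 | 79% | 79% | 80% |
| 0.55, 0.06 | 400 | 80% | 82% | 83% |
| 0.6, 0.1 | 600 | 69% | 72% | 74% |

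**5. The worst case.** HR 0.6, ICC 0.1, k = 20: 152.43 × 20 × 0.9/(20 − 15.243) = 576.8 per arm, and 2 × 576.8/0.85 = 1,357 enrolled. With whole numbers it is 1,368 (m = 29), or 1,404 if n is first rounded up to 153 (m = 30). Enrolling 864 in 40 facilities gives about 75%.

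**6. Unequal cluster sizes.** The design effect becomes 1 + ((1 + CV²) × mean size − 1) × ICC. The document gives no CV, so these are assumptions. For 600 residents, HR 0.6 and ICC 0.06 in 40, 45 and 50 facilities, CV 0.4 gives 76%, 79% and about 80%; CV 0.5 gives 75%, 77% and 79%.

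**The case against.** **No printed figure is wrong.** 180, 864 and about 300 all reproduce. This stands: there is no arithmetic error.

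**The protocol does not claim 80% power for HR 0.6 at 400–600.** A reader might infer that it does, since no other power is stated. The text ties the 80% to the uncorrected 180 per arm and says that a design effect then inflates that number. So the fault is that the text leaves the corrected power unstated.

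**HR 0.55 is one of the plan's own values.** A reader might take the lower end as resting on a shifted target. The section announces two values for the expected outcome and uses 0.6 and 0.55. At ICC 0.06 the range 400–600 roughly spans the two: HR 0.55 needs about 395 in 40 facilities, and HR 0.6 needs 568 in 45. That is a coherent rationale, but the text does not give it.

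**Fig. 3 is not shown.** It is described as covering scenarios for ICC and number of clusters, and may tabulate ICC 0.06 and 40 facilities. This limits the severity. It would not supply the missing link in the text or correct the label.

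**Worst case may refer to the ICC alone.** The sentence is about variation by ICC and states the 50 clusters openly, so nothing is hidden. But the same paragraph applies the same label to 20 clusters per arm, so 864 is not the worst case of the plan's own inputs.

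**The ICC of 0.06 is called conservative because it comes from three facilities.** Few clusters make an ICC imprecise. They do not make it too high, so this is no ground for planning below 0.06.

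**Conclusion.** The point holds, with moderate severity. At the protocol's own ICC and with equal cluster sizes, 80% power for HR 0.6 is reached only from about 532–554 residents (50 facilities) or 568–576 (45). With 40 facilities it takes 621–641, which is outside the planned range. At 400 residents power for HR 0.6 is 69–72%. That size supports about HR 0.55 at ICC 0.06, or comes to 79–80% for HR 0.6 if the ICC is 0.02.

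The quoted worst case of 864 understates the joint worst case of about 1,360–1,400. At ICC 0.1 even the planned maximum of 600 gives 69–74% for HR 0.6.

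The results rest on a constant hazard, 15% attrition removed from the sample, and the fixed-cluster design effect that reproduces 864. Unequal cluster sizes, which the protocol expects, lower every power; by how much depends on a CV that the document does not give. The documents do not support saying that the trial was sized by a wrong calculation, or that it claims a power it lacks.

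**What to change.** In the text of the sample size section:

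- State the power of the planned design after cluster correction. At ICC 0.06, 80% for HR 0.6 holds only from about 532–554 residents (50 facilities) to 621–641 (40 facilities), and 400 residents support about HR 0.55. If Fig. 3 already holds these cells, cite them.
- Restate the worst case as ICC 0.1 with 40 facilities (about 1,360–1,400), and say that the trial does not cover ICC 0.1 for HR 0.6.
- Add that unequal cluster sizes reduce these powers, with any CV marked as an assumption.
- Describe the ICC of 0.06 as imprecise rather than conservative.

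The cost is a few sentences and at most one small table. No extra residents or facilities are required. The downside is a less favourable stated power.
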